## Abstract

**Background:**

The Global Burden of Diseases, Injuries, and Risk Factors Study (GBD) collects and calculates risk-outcome data for modifiable lifestyle exposures (eg, dietary intake) and physical health outcomes (eg, cancers). These estimates form a critical digital resource tool, the GBD VizHub data visualization tool, for governments and policy makers to guide local, regional, and global health decisions. Despite evidence showing the contributions of lifestyle exposures to common mental disorders (CMDs), such as depression and anxiety, GBD does not currently generate these lifestyle exposure-mental disorder outcome pairings. This gap is due to a lack of uniformly collected and analyzed data about these exposures as they relate to CMDs. Such data are required to quantify whether, and to what degree, the global burden of CMDs could be reduced by targeting lifestyle factors at regional and global levels. We have established the Global burden of disease Lifestyle And mental Disorder (GLAD) Taskforce to address this gap.

**Objective:**

This study aims to generate the necessary estimates to afford the inclusion of lifestyle exposures as risk factors for CMDs in the GBD study and the GBD digital visualization tools, initially focusing on the relationship between dietary intake and CMDs.

**Methods:**

The GLAD project is a multicenter, collaborative effort to integrate lifestyle exposures as risk factors for CMDs in the GBD study. To achieve this aim, global epidemiological studies will be recruited to conduct harmonized data analyses estimating the risk, odds, or hazards of lifestyle exposures with CMD outcomes. Initially, these models will focus on the relationship between dietary intake, as defined by the GBD, and anxiety and depression.

**Results:**

As of August 2024, 18 longitudinal cohort studies from 9 countries (Australia: n=4; Brazil: n=1; France: n=1; Italy: n=3; The Netherlands: n=3; New Zealand: n=1; South Africa: n=1; Spain: n=1; and United Kingdom: n=3) have agreed to participate in the GLAD project.

**Conclusions:**

Our comprehensive, collaborative approach allows for the concurrent execution of a harmonized statistical analysis protocol across multiple, internationally renowned epidemiological cohorts. These results will be used to inform the GBD study and incorporate lifestyle risk factors for CMD in the GBD digital platform. Consequently, given the worldwide influence of the GBD study, findings from the GLAD project can offer valuable insights to policy makers worldwide around lifestyle-based mental health care.

**International Registered Report Identifier (IRRID):**

DERR1-10.2196/65576

## Introduction

Mental disorders rank among the top 10 leading causes of disease and economic burden worldwide. They account for 4.9% of global disability-adjusted life years [1] and it has been projected that by 2030 mental disorders will account for more than half of the economic burden attributable to noncommunicable diseases [2]. Given the recognized burden on individuals, communities, and economies [1,3], identifying risk factors for common mental disorders (CMDs), namely depression and anxiety disorders, is critical for early prediction, prevention, and treatment. While known risk factors such as genetics, childhood adversity, and family conflict have a significant impact on CMD risk [4], preventative efforts should also address potentially more modifiable factors that may have broader reach.

Over the past decade, evidence has emerged highlighting lifestyle behaviors as modifiable risk factors for CMDs. A recent meta-review, drawing from top-tier data such as meta-analyses of prospective cohort studies, Mendelian randomization studies, and randomized controlled trials, emphasized the significant role of lifestyle behaviors pertaining to diet quality, physical activity, smoking, and sleep in CMD risk [5]. Furthermore, current evidence indicates that targeting these lifestyle behaviors can ameliorate the risk of CMDs. For example, data involving adult participants from France estimate that 14% of incident cases of depression are attributable to a combination of unhealthful diet, weight, and smoking [6]. Promisingly, data from Norwegian adults show that 12% of de novo depression could be averted if an individual engages in at least 1 hour of physical activity per week [7]. Collectively, this evidence highlights the importance of lifestyle factors in mental health outcomes, which has implications regarding prevention and treatment.

Despite ample evidence supporting the inclusion of lifestyle-based mental health care in clinical recommendations and population-level strategies [8], exemplified by clinical practice guidelines from organizations such as the Royal Australian and New Zealand College of Psychiatrists [9], the global implementation of these strategies for addressing CMDs remains limited. Global nutritional recommendations focus largely on individual food groups or constituents, and not on the dietary patterns, such as the Mediterranean diet, that are commonly used in research. As such, the evidence regarding whether dietary components would be useful to the target population's mental health is unclear. Furthermore, it is widely acknowledged that numerous structural barriers hinder the improvement of lifestyle behaviors, including social, financial, and environmental determinants [10,11]. These barriers also exist in mental health treatment and care [12]. Therefore, there is merit in attempting to reduce the incidence of CMDs by improving lifestyle behaviors, not just at the individual level, but also through population and policy-level strategies. To inform such strategies worldwide, rigorous global data are required to quantify the contribution of lifestyle behaviors to the risk of population CMDs.

The largest epidemiological study worldwide, the Global Burden of Diseases, Injuries, and Risk Factors Study (GBD), provides important global health estimates that inform public health priority setting and policies. A critical tool used by the GBD to communicate the current state of health and disease for different countries is the digital platform, the GBD VizHub Data visualization tool [13]. This digital platform allows policy makers to quickly ascertain where the greatest improvements in public health could be achieved by targeting specific risk factors. The GBD currently provides comprehensive estimates of lifestyle risks, such as diet, for a range of physical conditions, but has yet to incorporate estimates of these lifestyle risks for CMDs. This may be due to challenges in operationalizing and standardizing the measurement of lifestyle factors and CMD outcomes across studies, aligning them with GBD classifications and definitions, and establishing clear cause-and-effect relationships, particularly given the typical clustering of lifestyle risk factors [14-16]. In addition, studies investigating the associations between lifestyle risk factors and CMDs often face issues such as a lack of global representation, small sample sizes, inconsistent methodologies, residual confounding, and measurement error, particularly in regard to measuring dietary intake or ensuring adherence in intervention studies [17]. Consequently, while these factors are well-recognized risk factors for physical illnesses like heart disease and diabetes, the potential for lifestyle targets to be considered relevant to the population’s mental health has historically been neglected [18].

To include lifestyle exposures as risk factors for CMDs on the GBD digital platform, the Global burden of disease Lifestyle And mental Disorder (GLAD) Taskforce (a large-scale, coordinated, international collaborative effort) has been formed. The Taskforce comprises global epidemiological experts who will work with GBD representatives to oversee the comprehensive evaluation of the association of lifestyle risk factors with CMDs, starting with dietary intake as the exposure of interest (the GLAD project). These experts have developed a harmonized approach for individual studies to conduct analyses (the GLAD project) to enable the integration of lifestyle factors as a risk for CMDs in the GBD. This paper outlines the processes by which the GLAD project and participant member studies will execute this harmonized data analysis protocol on their own datasets and disseminate their results through peer-reviewed publications. The overarching aim of the GLAD project is to generate robust, comparable evidence on the global risk of CMDs attributable to lifestyle factors, ultimately enabling their inclusion as risk factors for CMDs within the GBD framework. We hypothesize that more healthful lifestyle factors, such as higher intakes of healthful dietary components (eg, fruits, vegetables, whole grains, and fiber) will be associated with a lower risk of CMDs. Conversely, we hypothesize that less healthful lifestyle factors, such as higher intake of less healthful dietary components (eg, processed meat, sugar-sweetened beverages, and sodium) will be associated with a higher risk of CMDs.

## Methods

### Recruitment

The GLAD project is a collective, multistudy initiative led by Deakin University’s, Food and Mood Center, which is situated within the Institute for Mental and Physical Health and Clinical Translation, School of Medicine, Barwon Health, Geelong, Australia. The GLAD project will be completed by the GLAD task force, comprising the project team, the advisory group, and the working group containing all member studies (Figure 1).

**Figure 1 figure1:**
[figure not shown]
The GLAD taskforce composition and responsibilities within the GLAD project. GLAD: Global burden of disease Lifestyle And mental Disorders.

To identify potential member studies for participation in the GLAD project, which would apply the harmonized data analysis protocol to their own datasets and contribute their results to the broader initiative, we used a multistep process. The first step was to identify epidemiological studies that had the necessary variables by which the study lead or representative could execute our analysis plan (eg, food frequency questionnaires from which to derive GBD-defined dietary risks combined with mental health questionnaires to identify cases of depression or anxiety). This process involved a literature search to identify potentially eligible studies and key contacts to approach for invitation to participate in the GLAD project. To operationalize the dietary risk variables, we used previous GBD papers, which contained the definitions of each dietary exposure (Table 1) and depression and anxiety (Table 2) [1,19]. In addition to using the literature to identify potentially eligible datasets, we also drew on previous collaborations of the GLAD project team and researchers in the field of nutritional psychiatry (eg, via the International Society of Nutritional Psychiatric Research), as well as promoting the project on Food and Mood Center social media sites. Data custodians of identified studies were contacted, and those with relevant data and who had the capacity to participate in the GLAD project completed an expression of interest via the Food and Mood Center website.

To be eligible for inclusion, member studies must have dietary intake (Table 1) and depression and anxiety outcomes (Table 2) consistent with GBD definitions, or the ability to recode existing variables accordingly. Any deviations to these definitions must be reported and will be accounted for accordingly as reported below in “Future Directions: Meta-analyses.” Any study design, in any location, with any sample size, is eligible to be a member study and can complete the required data analysis.

**Table 1 table1:** Dietary exposure definitions and required coding for the GLAD project^a^.

Dietary risk factor	GBD^b^ exposure definition	Required coding^c^
Fruits	Average daily consumption of less than 310-340 g of fruit including fresh, frozen, cooked, canned, or dried fruit, excluding fruit juices and salted or pickled fruits.	grams/day
Vegetables	Average daily consumption of less than 280-320 g of vegetables, including fresh, frozen, cooked, canned, or dried vegetables and excluding legumes and salted or pickled vegetables, juices, nuts and seeds, and starchy vegetables such as potatoes or corn.	grams/day
Legumes	Average daily consumption of less than 90-100 g of legumes and pulses, including fresh, frozen, cooked, canned, or dried legumes.	grams/day
Whole grains	Average daily consumption of less than 140-160 g of whole grains from breakfast cereals, bread, rice, pasta, biscuits, muffins, tortillas, pancakes, and other sources.	grams/day
Nuts and seeds	Average daily consumption of less than 10-19 g of nuts and seeds.	grams/day
Milk	Average daily consumption of less than 360-500 g of milk including non-fat, low-fat, and full-fat milk, excluding plant derivatives.	grams/day
Red meat	Any intake of red meat including beef, pork, lamb, and goat but excluding poultry, fish, eggs, and all processed meats.	grams/day
Processed meat	Any intake of meat preserved by smoking, curing, salting, or addition of chemical preservatives.	grams/day
Sugar-sweetened beverages	Any intake of beverages with ≥50 kcal per 226.8-g serving, including carbonated beverages, sodas, energy drinks, and fruit drinks, but excluding 100% fruit and vegetable juices.	grams/day
Fiber	Average daily consumption of less than 21-22 g of fiber from all sources including fruits, vegetables, grains, legumes, and pulses.	grams/day
Calcium	Average daily consumption of less than 1.06-1.1 g of calcium from all sources, including milk, yogurt, and cheese.	grams/day
Seafood omega-3 fatty acids	Average daily consumption of less than 430-470 mg of eicosapentaenoic acid and docosahexaenoic acid.	milligrams/day
Polyunsaturated fatty acids	Average daily consumption of less than 7%-9% of total energy intake from polyunsaturated fatty acids.	total percentage of daily energy intake
Trans fatty acids	Any intake of trans fat from all sources, mainly partially hydrogenated vegetable oils and ruminant products.	total percentage of daily energy intake
Sodium	Average 24-hour urinary sodium excretion greater than 1-5 g.	grams/day
Ultra-processed foods (optional)	Any intake of ultraprocessed foods, as defined by the Nova system as any food item in Nova category 4 (“ultraprocessed food”), in grams [20].	grams/day

^a^Based on the GBD (Global Burden of Diseases, Injuries, and Risk Factors Study) risk exposure definitions (Pages 217-218 in Supplementary Appendix 1 in the study by the the GBD 2019 Risk Factors Collaborators [19]).

^b^GBD: Global Burden of Diseases, Injuries, and Risk Factors Study.

^c^Analyses using continuous exposures are required by the GLAD Taskforce. The units listed here are recommended, however, these may be rescaled to more meaningful units in papers (eg, per 10 g) provided the original units are available to the project team.

**Table 2 table2:** Mental health definitions and recommended coding for the GLAD^a^ project^b^.

Mental disorder	Outcome definition	Diagnostic reference	Recommended coding^c^
Major depressive disorder	Involves the presence of at least one major depressive episode, which is the experience of either depressed mood or loss of interest/pleasure, for most of every day, for at least two weeks.	DSM-IV-TR^d^: 296.21–24; 296.31–34. ICD-10^e^: F32.0-9; F33.0-9.	0=no MDD^f^; 1= MDD
Anxiety disorders (any subtype)	Involves experiences of intense fear and distress, typically in combination with other physiological symptoms. Anxiety disorders will be modeled as a single cause for “any” anxiety disorder to avoid the double-counting of individuals meeting criteria for more than one anxiety disorder. Epidemiological estimates reporting an outcome for “any” or “total” anxiety disorders will be included if they reported on at least three anxiety disorders.	DSM-IV-TR: 300.0-300.3; 208.3; 309.21; 309.81. ICD-10: F40-42; F43.0; F43.1; F93.0-93.2; F93.8.	0=no anxiety disorder; 1=anxiety disorder

^a^GLAD: Global burden of disease Lifestyle And mental Disorders.

^b^The definitions and diagnostic references presented in this table are the current definitions used by the GBD (Page 4 in the Supplementary Appendix in the study by the GBD 2019 Mental Disorders Collaborators [1]). Since GLAD members may use alternative methods to ascertain disorder status, definitions or diagnostic references may vary slightly. For example, somatic forms of depression may be captured more by symptom scales, or studies using prescriptions may use Anatomical Therapeutic Chemical codes to determine incident depression and anxiety.

^c^Outcomes must be binary (condition present vs condition absent). For studies that only use symptom scales, validated cutoffs can be used to determine condition present versus condition absent (refer to Multimedia Appendix 1).

^d^*DSM-IV-TR*: *Diagnostic and Statistical Manual of Mental Disorders (Fourth Edition, Text Revision)*.

^e^*ICD-10*: *International Statistical Classification of Diseases, Tenth Revision*.

^f^MDD: major depressive disorder.

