#### Covariates and Confounders

To address the anticipated heterogeneity of member studies’ available data, a set of core confounders are provided for the purpose of generating a consistent minimally adjusted analysis. The conduct of additional analyses (eg, using additional variables, fitting sensitivity models, or exploratory analyses) is at the discretion of the study author or authors based on available data and reviewer requests when studies are submitted for publication.

To be included in the GLAD project, member studies must adhere to the iteratively adjusted models (Textbox 1).

The iteratively adjusted statistical models required for the Global burden of disease Lifestyle And mental Disorders (GLAD) task force.Model 1: Unadjusted model, with the dietary variable (as listed in Table 2) as the exposure and depression or anxiety as the outcome.Model 2: Minimally adjusted model, with the dietary variable of interest, depression or anxiety, and with baseline mental disorder status (or lifetime history of mental disorders for cross-sectional studies), age, sex, and a measure of socioeconomic status, such as household income, employment status, or education.Sensitivity model: Same as model 2, but with adjustment for total energy intake.

Of particular relevance in nutritional epidemiology are methods for adjusting for energy intake. Intake of specific nutrients are correlated with total energy intake, and so appropriate adjustment is required to disentangle the effect of the nutrient from the effect of energy. For example, an individual may alter intake of a specific nutrient by changing dietary composition, and not by changing total energy intake. As such, controlling energy intake can reduce confounding, and failure to appropriately control for total energy intake may nullify associations between nutrient intake and disease outcomes [27]. Given the correlation between nutrient intake and energy, the application of Willett’s residual method is recommended to account for total energy intake [27]. This involves fitting a regression model with the dietary variable as the outcome and total energy intake as the exposure, predicting residuals from this model, and then using these predicted residuals in the analysis models [27].

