#### Estimating Risk Ratios, Odds Ratios, and Hazards Ratios

Each study is required to use risk ratios (estimated by Poisson regression with robust SE) as the primary means of assessing the association of dietary intake with CMDs. Risk ratios are based on incident cases, and so models will need to exclude participants with depression or anxiety at baseline. Furthermore, to determine incident risk, studies must have dietary exposures at baseline and depression, or anxiety measured at a subsequent time point. Where the estimation of a risk ratio is not possible (refer to Figure 2), for example, where the total number of people exposed at baseline is not available (such as for retrospective or case-control studies) [29], odds ratios are estimated using standard logistic regression techniques. Where only time-to-event data are available, hazard ratios are used, estimated by a Cox proportional hazards model. For rigor, all effect estimates will be accompanied by a 95% CI and exact *P* value [30].

Models can be fitted using any statistical analysis software, including R (R Core Team), SAS/STAT (SAS Institute Inc), Stata (StataCorp LLC), and SPSS (IBM Corp). Before fitting the relevant models, Member studies must assess model assumptions. Should any model assumptions be violated, an alternate approach to analysis may be selected. For example, the nonlinearity of continuous variables should be investigated, and transformations or nonlinear models fitted where necessary. Similarly, should any of the assumptions of Cox proportional hazards models be violated, alternative strategies will be deployed to account for these violations.

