In addition to the models listed above, the following subgroups shall be fitted separately for each exposure-outcome pairing, where data allows: (1) sex, (2) age, (3) year (for longitudinal studies with multiple waves of follow-up), (4) country (for multicenter studies), and (5) all symptom scales and diagnostic measures (for studies with depression and anxiety measured via multiple measures. For age, studies should explore the relationship between the risk factors and mental disorders with age to see if a continuous measure is appropriate. Where a continuous measure is not appropriate, studies should generate appropriate age categories for their dataset by inspecting the frequency of outcomes by age groups. As a guide, the GBD currently uses 0-6 days (early neonatal), 7-27 days (late neonatal), 28-365 days, 1-4 years, 5-9 years, then 5-year intervals from 10-95 [31].

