### Strengths and Limitations

Currently, the GBD is unable to include lifestyle exposures such as dietary intake as a risk for CMDs due to the following: difficulties determining directionality and causality, inconsistency in dietary variables and methods, small sample sizes, and lack of global representation. A strength of the GLAD project is that it will address all these methodological considerations. We will (1) prioritize prospective studies using incident cases (ie, excluding those with baseline CMDs) to obtain risks of CMDs attributable to dietary intake, and not the other way around (to determine directionality or temporality), (2) include all study designs (including from experimental or randomized controlled trials to strengthen causal conclusions), (3) conduct harmonized data analyses approved by the GBD (to improve consistency between studies and specificity of the diet-CMD relationship), and (4) pool data from multiple studies from around the world (to address sample size and global representation).

Despite the clear strengths of the GLAD project, there are some limitations. First, the GBD study is an ongoing and dynamic study, and definitions and methods are constantly evolving. Every effort will be made to ensure the taskforce are following GBD-approved methods, however, some changes from the GBD may be unavoidable. Second, since the GBD does not currently include ultraprocessed food as a dietary risk factor, the definitions and methods used by the task force may not reflect those used in future iterations of the GBD. Finally, although food intakes provide a general overview of diet quality, people do not eat food items in isolation. The current methods used by the GBD do not currently consider dietary patterns. This may limit interpretations to specific food items and not to an overall dietary pattern.

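### In symptom-scale studies, people on current antidepressant or anxiolytic treatment who score below the cutoff stay in the incident risk set, so some counted incident cases may be relapses

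*Protocol article*

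**What the plan says.** The relevant rules stand in four places of the protocol article.

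- **Case status (Table 2, footnotes b and c).** Footnote c requires a two-level outcome: "Outcomes must be binary (condition present vs condition absent"). It continues: "For studies that only use symptom scales, validated cutoffs can be used to determine condition present versus condition absent". Footnote b accepts other sources, so that "studies using prescriptions may use Anatomical Therapeutic Chemical codes to determine incident depression and anxiety", and describes the resulting differences thus: "definitions or diagnostic references may vary slightly".
- **Risk set (Estimating Risk Ratios, Odds Ratios, and Hazards Ratios).** "Risk ratios are based on incident cases, and so models will need to exclude participants with depression or anxiety at baseline". No instrument is named for that exclusion, and current treatment is not mentioned.
- **Adjustment (Covariates and Confounders, Model 2).** The required set is "baseline mental disorder status (or lifetime history of mental disorders for cross-sectional studies), age, sex, and a measure of socioeconomic status". Lifetime history is therefore named only for cross-sectional designs, while Results reports that all 18 recruited studies are longitudinal.
- **Purpose (Strengths and Limitations).** To settle the direction of effect, the project will "prioritize prospective studies using incident cases (ie, excluding those with baseline CMDs").

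**The concern.** A cutoff score measures current symptoms. Someone whose depression is controlled by medication can score below it and still have the disorder. Under a cutoff-only rule that person passes the baseline exclusion and enters follow-up as disease-free. If symptoms return, the event is counted as new onset.

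Two things are at stake. First, people with existing illness may eat differently because of it, and the baseline exclusion is the protocol's main device against that reverse direction. The device fails for treated disease. Second, the same person can be coded 0 in a scale-based study and 1 in a prescription-based study, which is more than a slight variation between member studies.

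A related question arises at follow-up: a person who becomes ill, is treated and responds may score below the cutoff and count as a non-case.

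**Working it through.** **Reading the rules together.** The document states no figure to reproduce on this point.

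1. The cutoff rule contains no treatment term.
2. In a study whose only measure is a scale, the baseline exclusion can use only that cutoff status, so treated people below the cutoff remain.
3. Model 2's baseline status, if taken from the same cutoff, has a single value once baseline cases are excluded. It then adjusts for nothing.
4. The checks by ascertainment type (Exposure and Outcome Definitions) and the cross-walking (Future Directions: Meta-Analyses) compare study results. They cannot take people out of a risk set whose model is already fitted.

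**Illustration of size.** Every input is an assumption; none comes from the document.

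- p = 6%: incident risk in untreated, truly disease-free people with the better diet
- t = 2% to 10%: share of the better-diet risk set that is treated and below the cutoff
- q = 20% to 40%: later above-cutoff risk in those treated people, taken as the same in both diet groups
- k: ratio of t in the poor-diet to the better-diet group
- R: true risk ratio

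Observed risk, better diet: (1 − t)p + tq. Observed risk, poor diet: (1 − kt)pR + ktq.

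*Share of counted cases that are relapses (better-diet group)*, tq / [(1 − t)p + tq]:
- t = 2%, q = 20%: 0.0040 / (0.0588 + 0.0040) = 6.4%
- t = 10%, q = 40%: 0.040 / (0.054 + 0.040) = 42.6%

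*Observed risk ratio:*

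| True R | k | Observed range |
|---|---|---|
| 1.00 | 1.00 | 1.00 |
| 1.00 | 1.25 | 1.01 to 1.09 |
| 1.00 | 1.50 | 1.02 to 1.18 |
| 1.20 | 1.00 | 1.12 to 1.19 |

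For example, with R = 1.00, k = 1.5, t = 10% and q = 40%, the poor-diet risk is 0.85 × 0.06 + 0.15 × 0.40 = 0.111, and 0.111 / 0.094 = 1.18.

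The sign reverses if treatment is less common with a poor diet. With R = 1.00 and k = 0.8:
- t = 10%, q = 40%: (0.92 × 0.06 + 0.08 × 0.40) / 0.094 = 0.0872 / 0.094 = 0.93
- t = 2%, q = 20%: (0.984 × 0.06 + 0.016 × 0.20) / 0.0628 = 0.06224 / 0.0628 = 0.99

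**Follow-up.** Take true risks of 6.0% and 7.2% (ratio 1.20) and perfect specificity.
- Equal sensitivity of 0.8 or 0.6 in both groups: the ratio stays at 1.20; only the better-diet risk falls, to 4.8% or 3.6%.
- Sensitivity 0.7 with the better diet and 0.8 with the poor diet: 0.072 × 0.8 / (0.06 × 0.7) = 1.37.
- Reversed: 0.072 × 0.7 / (0.06 × 0.8) = 1.05.

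All of this uses two diet groups without covariates. The protocol requires continuous exposures and a socioeconomic covariate, so these figures show orders of size and are not predictions.

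**The case against.** The other side has good points.

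- **The rule is permissive.** Footnote c says cutoffs can be used and limits this to studies with symptom scales only. The baseline exclusion names no instrument, so a study with medication records may already exclude treated people. This stands: the text leaves the matter open and does not prescribe the wrong answer. But in a plan meant to harmonise analyses, leaving it open lets studies differ on who is at risk.
- **Mitigations exist.** Recruitment requires deviations from the definitions to be reported. Covariates and Confounders allows additional variables and sensitivity models at the authors' discretion. A sensitivity analysis by ascertainment type is possible, and phase 3 plans meta-regression and cross-walking. These partly answer the mismatch between studies, but they do not require any single study to repair its risk set.
- **Socioeconomic adjustment** may absorb part of any link between diet and treatment uptake. This stands, and it limits the size.
- **Unseen material.** Multimedia Appendix 1 and the Open Science Framework registration are not shown. A treatment rule there cannot be ruled out, although the appendix title covers only tools, scales and cutoffs. Results, however, describes harmonisation as following the analysis plan given in this article.

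A reader might infer two stronger claims. One is that the protocol forbids combining scale and treatment data, because it asks for separate models for "all symptom scales and diagnostic measures (for studies with depression and anxiety measured via multiple measures"). It does not: those models come on top of the main ones, and nothing bars a combined main definition. The other is that associations will be inflated. The document gives nothing to support that; the calculations go either way. It is also hard to assume both that treated status is more common with a poor diet at baseline and that treatment reaches fewer poor-diet cases at follow-up, unless disease itself differs strongly by diet.

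**Conclusion.** The point holds for the baseline risk set. In scale-based studies the cutoff rule and the baseline exclusion, read together, can leave treated prevalent patients among those counted as at risk. Some incident cases may then be relapses, and the directionality claim is weaker than stated. Model 2 does not help when baseline status rests on the same cutoff.

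Size and direction are uncertain because the document supplies no inputs. If treated status is unrelated to diet, there is no spurious association; a true effect is attenuated, provided diet does not alter relapse risk to the same degree. If treated status is more common with a poor diet, a modest spurious ratio of about 1.01 to 1.18 arises under the assumed inputs, and if it is less common the bias runs the other way. Under-counting treated cases at follow-up is the weaker part: it biases the ratio only if it differs by diet or specificity is imperfect.

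**What to change.** Add to Estimating Risk Ratios, Odds Ratios, and Hazards Ratios:

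1. Scale-based studies that hold medication data, or a recorded prior diagnosis, report the incident model with current antidepressant or anxiolytic users (or those with the recorded diagnosis) excluded at baseline. This should be at least a required sensitivity model beside the cutoff-only model.
2. Every study records which baseline and follow-up case rule it used, so that the phase 3 cross-walk can use it.

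A follow-up outcome of above cutoff or newly treated may be offered as optional. It should be labelled as not matching the separate depression and anxiety outcomes in Table 2, since these drugs do not identify which disorder is present.

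The cost is one eligibility line and one additional model in studies that already hold the data; studies without such data only state that they lack it. The drawbacks are a slightly smaller analysed sample and the exclusion of some people who take these drugs for other indications. The change has to be made before member studies finish phase 2, because pooled estimates cannot be corrected for it afterwards.
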